### Data analysis

Quantitative statistics will be summarised as mean and standard deviation (SD) or median and interquartile range (IQR) for normally and non-normally distributed continuous data, respectively, or frequency and percentage for categorical data at baseline, three-, six-, and 12-month post randomisation by treatment arms. Descriptive statistics will be presented by treatment arms. Data will be assessed for normality using the Shapiro-Wilks test to assess for heterogeneity between groups, baseline values will be compared using independent t-tests or Wilcoxon signed rank tests. Data regarding the number of participants expressing interest, eligible, consented, withdrawn, and lost to follow-up, as well as adherence to remotely prescribed exercise (for intervention arm) and outcomes assessments, will be summarised by treatment arms. Differences in mean outcomes between treatment arms at three-, six-, 12-month post-randomisation, and the difference of the change from baseline to three-, six-, 12-month post-randomisation between arms will be calculated and assessed using a mixed model ANOVA. Assuming the data meet the assumptions of an ANOVA, post hoc tests will be conducted on significant differences. Partial eta squared will be reported as effect sizes. All estimates will be reported with a 95% confidence interval. The alpha level will be set at 0.05. No formal hypothesis testing will be performed. Analysis and reporting of the MAINTAIN trial will be in line with the CONSORT statement.^52^ All primary analyses are planned to be on an intention-to-treat basis with a secondary per protocol analysis. The ADePT (A Process for Decision-making after Pilot and Feasibility Trials)^53^ framework will be used to identify and examine any problems which arise with the methodology. This appraisal of this study will help to find solutions to problems that arise and influence the process of progressing to a definitive RCT. All statistical analysis will be undertaken using IBM SPSS software.

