The MAINTAIN trial aims to examine the feasibility of a long-term exercise and PA maintenance programme, which is remotely prescribed and monitored using a wearable activity device with real-time biometrics and haptic feedback, alongside personalised text messaging in people with CHD. MAINTAIN will address PA behaviours, exercise adherence, and a variety of health-outcomes over a 12-month period. The study will also aim to identify a primary outcome for a future definitive trial and provide additional evidence to fill key gaps in the literature relating to long-term health outcomes.^55^ This feasibility study aims to tackle an important and complex problem by taking a multi-faceted approach to improving long term adherence to exercise after completion of CR. Both qualitative and quantitative data will be collected to examine the acceptability of the intervention, and interviews will help to inform patient and public involvement and engagement for a future definitive RCT. To minimise the effects of both bias and attrition, as reported in a previous systematic review,^55^ the MAINTAIN trial will blind outcomes assessors and apply an intention to treat analysis. Adverse events will be reported according to trial arm.

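### The arm comparisons do not adjust for baseline, and the ANOVA named may drop participants with a missed visit; a baseline-adjusted mixed model would give tighter estimates at almost no cost

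*Protocol article*

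**What the plan says.** The Data analysis section of the protocol article names two contrasts. The first is "Differences in mean outcomes between treatment arms at three-, six-, 12-month post-randomisation". The second is "the difference of the change from baseline to three-, six-, 12-month post-randomisation between arms". These differences "between arms will be calculated and assessed using a mixed model ANOVA". The section then adds that "Partial eta squared will be reported as effect sizes", that estimates will carry 95% confidence intervals, and that "All statistical analysis will be undertaken using IBM SPSS software". No baseline covariate is mentioned. Baseline values are instead compared between arms in a separate test.

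The Sample size section describes the design as a repeated measures ANOVA with two groups and four timepoints. With assessments at baseline and at 3, 6 and 12 months, baseline is one of those four.

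On the analysis population, the Data analysis section says: "All primary analyses are planned to be on an intention-to-treat basis with a secondary per protocol analysis". The Discussion gives the purpose, "To minimise the effects of both bias and attrition", and says that "the MAINTAIN trial will blind outcomes assessors and apply an intention to treat analysis".

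**The concern.** There are two separate issues.

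**Baseline.** A raw follow-up comparison makes no use of the baseline value. A change score subtracts it in full, whatever its correlation with follow-up. With 15 per arm, chance imbalance at baseline passes into the first and is over-corrected in the second. A baseline test between arms does nothing to correct it. Two parallel contrasts with no lead also leave open which estimate is the trial's answer for each outcome.

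**Missed visits.** Several features point to the classical between-within ANOVA: a repeated measures ANOVA in the sample size section, partial eta squared, ANOVA assumptions followed by post hoc tests, and SPSS. In SPSS that routine is the general linear model repeated-measures procedure, which uses only participants with a value at every timepoint. If it is used, those who miss a visit leave the analysis, although the Discussion relies on intention-to-treat to limit the effect of attrition.

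The trial is meant to help choose a primary outcome and estimate a sample size for a definitive trial. Interval width and selective loss of participants bear directly on those uses.

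**Working it through.** **1. The plan's own figure.** Inputs from the Sample size section: two groups, m = 4 timepoints, effect size 0.5, alpha 5%, and the stated beta of 90% read as power. The document gives no correlation, so 0.5 is assumed.

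- Between-arm test: noncentrality = N·f²·m / (1 + (m−1)ρ). With N = 30 and f = 0.5 this is 30 × 0.25 × 4 / 2.5 = 12. On 1 and 28 degrees of freedom, power is 0.917.
- Arm-by-time interaction: noncentrality = N·f²·m / (1−ρ). With f = 0.25 this is 30 × 0.0625 × 4 / 0.5 = 15. On 3 and 84 degrees of freedom, power is 0.903.

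Both readings return a total of 30, and N = 28 falls short of 0.90 in each (0.896 and 0.879). So the sample size matches a classical four-level repeated measures ANOVA with baseline as one of the levels.

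**2. Precision at one follow-up visit.** Inputs: n = 15 per arm (document) and baseline-to-follow-up correlation ρ (assumed, 0.3 to 0.9). In SD units the half-width is t × √(2/15 × k). The variance factor k is 1 for raw means, 2(1−ρ) for change and 1−ρ² for baseline-adjusted. t is 2.048 (28 df) for the first two and 2.052 (27 df) for the third.

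| ρ | Raw | Change | Baseline-adjusted |
|---|---|---|---|
| 0.3 | 0.75 | 0.89 | 0.71 |
| 0.5 | 0.75 | 0.75 | 0.65 |
| 0.7 | 0.75 | 0.58 | 0.54 |
| 0.9 | 0.75 | 0.33 | 0.33 |

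Example at ρ = 0.5: raw and change both give 2.048 × √(0.1333) = 0.748. Adjusted gives 2.052 × √(0.1333 × 0.75) = 0.649.

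Estimating the baseline slope from 30 people adds a small penalty, a variance factor of 1 + 1/26. The adjusted half-widths then become 0.73, 0.66, 0.55 and 0.33. The ordering does not change: adjustment is never wider than raw or change at any of these correlations.

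In large-sample terms the adjusted variance is 25% below both alternatives at ρ = 0.5. At ρ = 0.7 it is 49% below raw and 15% below change.

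**3. Missed visits, if the classical routine is used.** The document gives no loss rate. Assume independent loss of 5%, 10% or 15% at each of three follow-ups. The complete fraction is 0.95³ = 0.857, 0.90³ = 0.729 or 0.85³ = 0.614, so about 26, 22 or 18 of 30 remain.

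**4. Gain from keeping incomplete participants.** This was simulated with 15 per arm, 20% dropout by 12 months (assumed) depending on the previous value, and a longitudinal model with known covariance. Standard errors of the 12-month arm difference, in SD units:

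| ρ | Completers, change | Completers, adjusted | All available data |
|---|---|---|---|
| 0.5 | 0.423 | 0.377 | 0.361 |
| 0.7 | 0.319 | 0.303 | 0.290 |

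Using all data lowers the standard error by about 4% against adjusted completers (0.361/0.377 and 0.290/0.303). Against completer change scores it falls by 15% and 9% (0.361/0.423 and 0.290/0.319). Because the covariance was treated as known, these gains are slightly flattering.

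**The case against.** Much of the opposing case stands.

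- **Baseline is used.** A reader might infer that the plan ignores baseline. It does not, because the change score uses it. In a randomised trial a change-score comparison is unbiased and merely less efficient, and at high correlation the loss is negligible. What remains is the lack of covariate adjustment.
- **Case deletion is not written down.** A reader might infer that the plan contradicts its own intention-to-treat statement. That needs two stated positions, and only one is stated. The phrase mixed model could mean a likelihood-based model that keeps incomplete participants, and SPSS can fit one. The classical routine is the likelier reading but still an inference. An article may also leave missing-data methods to a fuller plan, so their absence is not a fault in itself.
- **Power is the wrong yardstick.** A reader might infer that the chosen model halves power, since a constant 0.5 SD effect at ρ = 0.5 has about 25% power on the interaction test and about 53% on a baseline-adjusted average of follow-ups. That sets a 3-df test against a 1-df contrast. The unadjusted 1-df contrast already has about 37%. The remedy below reports differences by visit, not that average, and the plan disclaims formal hypothesis testing.
- **The consequence is limited.** These outcomes are secondary in a 30-person feasibility trial. Means and SDs by arm and visit are promised anyway, as are arm differences with 95% intervals, so partial eta squared is an addition to them and not a substitute.

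None of this defends leaving baseline out as a covariate. The plan makes estimation its purpose, which makes interval width the relevant measure.

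**Conclusion.** The point holds as a recommended improvement. The analysis the article specifies is less precise than one that adjusts for a baseline value already collected. The half-width at one visit falls from 0.75 to 0.65 SD (0.66 with the small-sample penalty) at an assumed correlation of 0.5. At 0.7 it falls from 0.58 for change scores to 0.54 (0.55), and at 0.9 the advantage over change scores all but disappears. The correlation is not in the document, so the gain is a range.

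On missed visits the finding is conditional. If the classical repeated-measures routine is meant, participants with any missing visit drop out, and that is in tension with the intention-to-treat commitment. If a likelihood-based mixed model is meant, the tension goes away and only the wording needs clarifying. The counts of 26, 22 or 18 rest on both that reading and the assumed loss rates. No size can be put on any resulting bias from the document.

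**What to change.** Replace the two contrasts with one model per continuous outcome. This would be a linear mixed model (SPSS MIXED) fitted to all observed 3-, 6- and 12-month values, by allocated arm, with arm, visit, arm-by-visit and baseline value as fixed effects. Use an unstructured within-participant covariance, and name in advance a simpler structure to use if it does not converge with 30 participants.

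Report the adjusted mean difference with 95% confidence interval at each visit as the effect measure, in place of partial eta squared. State that participants with a missed visit stay in the model through the values they have. Someone with no follow-up value at all still contributes nothing to the arm difference, so report their number by arm.

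The cost is rewording a few sentences, slightly more modelling work and the pre-stated covariance fallback. No extra data, visits or software are needed.

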### Sample size

The MAINTAIN feasibility RCT will assess recruitment rate, adherence, acceptability, and clinical, physiological, and health-related outcomes. The study also aims to identify a primary outcome and estimate a sample size to inform a future definitive RCT based on long-term exercise adherence and health outcomes between the two treatment arms.^48^ However, assuming a medium effect size (0.5) for a repeated measures ANOVA, between two groups over four timepoints with an alpha of 5% and a beta of 90%, a total of 30 participants would be required.^49,50^ Due to the novelty of the proposed outcome measures, a medium effect size will be applied.^51^

From local data (UHCW NHS Trust), 255 patients per year have been identified as accessing community CR of which 212 have a diagnosis of coronary heart disease (CHD). Over a 24-month recruitment period, this provides a potential pool of 510 patients. Local audit data suggests at least 83% of these patients are eligible. Therefore, of these 510 local patients, 423 are potentially eligible, of which we aim to recruit 30 (i.e., approximately 7%, at an approximate rate of five per month).

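### The Data analysis section rules out hypothesis testing but also sets alpha at 0.05, triggers post hoc tests on significance and tests baseline differences; the text should settle on one approach

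*Protocol article*

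**What the plan says.** All the conflicting instructions but one are in a single paragraph of the protocol article, under Data analysis:

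- On the alpha level and on testing in general: "The alpha level will be set at 0.05. No formal hypothesis testing will be performed".
- On follow-up differences and differences in change from baseline, these "between arms will be calculated and assessed using a mixed model ANOVA".
- On what follows from the ANOVA: "Assuming the data meet the assumptions of an ANOVA, post hoc tests will be conducted on significant differences".
- On baseline: "baseline values will be compared using independent t-tests or Wilcoxon signed rank tests".

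The Sample size section then rests the number of participants on a test. For a repeated measures ANOVA with two groups, four timepoints and an effect size of 0.5, it states: "with an alpha of 5% and a beta of 90%, a total of 30 participants would be required".

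Three other statements bear on the point. The Data analysis section promises a 95% confidence interval for every estimate and names the ADePT framework for appraising progression. The Outcome measures section makes feasibility the primary outcome, and lists the physiological, clinical and patient-reported outcomes there as a means of identifying the definitive trial's primary outcome. The Sample size section adds that the study should help estimate that trial's sample size.

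**The concern.** An alpha level serves to declare a test result significant, and a step that depends on significance cannot run unless a test has been done. An analyst who obeys the no-testing sentence must ignore the alpha level, the post hoc rule and the baseline tests. An analyst who obeys those must ignore the no-testing sentence. A separate analysis plan could not merely complete this text: it would have to breach one instruction to honour the other.

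What is at stake is the use of the secondary outcomes. They are meant to inform the choice of the next trial's primary outcome and its size, and no sentence says that p-values will play no part. With 15 per arm and many outcomes, an outcome that crosses 0.05 may do so by chance, or with an estimate larger than the truth. Carrying that outcome and that estimate forward could leave the definitive trial with the wrong endpoint or too few participants.

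**Working it through.** **1. The plan's own figure.** Inputs from the Sample size section: 2 groups, 4 timepoints, effect size 0.5, alpha 5%, and a stated beta of 90%, read here as 90% power. The article gives neither the effect-size metric nor the within-person correlation ρ. I assume ρ = 0.5 and sphericity, and use noncentral F power.

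- Between-groups factor, f = 0.5: λ = f²·N·m / (1 + (m − 1)ρ) = 0.25 × 30 × 4 / 2.5 = 12, on 1 and 28 degrees of freedom. Power is 0.917, and 30 is the smallest even N reaching 90%. For ρ from 0.3 to 0.8, the required N runs from 24 to 38.
- Group-by-time interaction, f = 0.25 (the conversion of d = 0.5): λ = f²·N·m / (1 − ρ) = 0.0625 × 30 × 4 / 0.5 = 15, on 3 and 84 degrees of freedom. Power is 0.903, and N = 30 again. For ρ from 0.3 to 0.8, the required N runs from 42 down to 14.

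So 30 can be reproduced as the size for a powered significance test. The testing framework therefore appears in the design as well as in the analysis paragraph.

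**2. Side by side.** Of the instructions in the Data analysis section, the confidence intervals and the calculation of arm differences are compatible with the no-testing sentence. The alpha level, the trigger "post hoc tests will be conducted on significant differences" and the baseline t-tests or Wilcoxon tests are not. This conflict needs no arithmetic.

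**3. False positives if the testing rules are followed.** I count 10 secondary outcomes from Table 1 and the Assessments section: ISWT, physical activity, sedentary behaviour, SMART score, MacNew, PHQ-9, GAD-7, GSE, PAM and EQ-5D-5L. With one test each at 0.05 and no true effect:

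- Independent outcomes: 1 − 0.95¹⁰ = 0.40.
- Equal correlation between outcomes of 0.3: about 0.35 by simulation (15 per arm, 10,000 replicates).
- Equal correlation of 0.5: about 0.30 by simulation.

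The correlations are assumptions; the article gives none. If each outcome were tested at all three follow-ups there would be 30 tests, with 30 × 0.05 = 1.5 false positives expected.

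**4. Size of difference needed for significance.** With 15 per arm and complete data, an unadjusted difference at one visit reaches p < 0.05 at t(0.975, 28) × √(2/15) = 2.048 × 0.365 = 0.75 SD. This is also the half-width of the 95% confidence interval.

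For change from baseline, the threshold in units of the raw SD is 0.748 × √(2(1 − ρ)), where ρ is here the correlation between baseline and follow-up:

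- ρ = 0.5: 0.75 SD
- ρ = 0.7: 0.58 SD
- ρ = 0.8: 0.47 SD

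**The case against.** The best defence is that the sentence means no confirmatory testing, with alpha included only to match the 95% confidence intervals. That could explain the alpha level. It does not explain post hoc tests that start only after a significant result, nor the tests at baseline.

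Other objections do limit the point, because several stronger readings are tempting and the document does not support them.

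- A reader might infer that only contrasts following a significant ANOVA will be shown, so that the published estimates are selected on size. The Data analysis section says that the differences at three, six and 12 months will be calculated and that all estimates will carry a 95% confidence interval. Only the post hoc tests are conditional.
- A reader might infer that a chance p-value will become the trial's conclusion. Feasibility is the primary outcome, ADePT is the named framework for progression, and no p-value rule is stated.
- A reader might say that any true 0.5 SD effect found significant is overstated by at least half. That follows from the 0.75 SD threshold for an unadjusted contrast at one visit. For change from baseline, the minimum overstatement is about 16% at ρ = 0.7 (0.58/0.5), and none is forced at ρ = 0.8. The planned gate is also a mixed ANOVA, not a single-visit t-test.
- A reader might count 12 to 20 outcomes and quote 46% to 64% for at least one false positive. Those figures require independence, and the depression, anxiety and quality-of-life scales are plausibly correlated.

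**Conclusion.** The contradiction stands on the wording alone. The Data analysis section gives instructions that cannot all be followed, and the Sample size section reinforces the testing side.

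The consequence is moderate. Following the testing rules gives roughly a 30% to 40% chance of at least one false positive. This assumes 10 outcomes, one test each, no true effects and correlations between outcomes from 0.5 down to 0. An unadjusted single-visit difference would need to reach about 0.75 SD, assuming 15 per arm with complete data. The risk falls on the choice of the definitive trial's primary outcome and sample size. It does not touch the feasibility outcomes, randomisation or data collection. It should be fixed, and rewording before analysis is enough.

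**What to change.** Preferred change:

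- Data analysis: keep the statement that no formal testing will be done. Delete the alpha level, the significance-triggered post hoc tests and the baseline significance tests.
- Data analysis: state that the arm differences already planned, with 95% confidence intervals at three, six and 12 months, will be reported for every secondary outcome whatever their size.
- Sample size: present 30 as a number chosen for feasibility, not as power for an efficacy test.
- State that conclusions rest on the feasibility outcomes.

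Alternative, if the sponsor wants tests: delete the no-testing sentence, label the tests exploratory, and state that p-values will neither support efficacy claims nor select the definitive trial's primary outcome.

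The cost is a few sentences of rewording. The report would contain no p-values, or only exploratory ones. No data collection changes.

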### Embedded qualitative study

Semi-structured interviews will be conducted with 10 participants from both the intervention and control group at three-, six-, and 12-months, and with participants who drop out. The 10 interviewed participants will remain the same throughout all follow-ups. It will not be possible to replace dropouts with additional participants. Interviews will take place via online video call, face-to-face, or phone call, and will be recorded, pseudonymised, and transcribed verbatim. Questionnaires will be offered to those who chose not to participate.

*Qualitative analysis*. Data will be analysed using thematic analysis^54^ in an inductive approach using NVivo^©^ (QSR International Pty Ltd, Chadstone, VIC, Australia) software to allow rich and detailed information regarding the acceptability of the trial, Polar Ignite watch and intervention. Data will be analysed in the following steps:
Data familiarisation: reading and listening to complete interview transcripts, audio recordings and field notes.Generate initial codes: transcripts will be coded, and key concepts identified.Searching for themes: codes will generate themes and subthemes as an output from the data to develop an initial thematic map.Reviewing themes: codes included in generated themes will be checked to ensure they create a pattern, and the validity of the themes will be reviewed to ensure they represent the whole data set.Defining and naming themes: each theme will be defined succinctly, and possible subthemes will be reviewed before naming the theme.Producing the report: data will be analysed and written up.Both qualitative and quantitative data will be synthesised to integrate the overall results. Comparing both data types of data will reveal any differences or agreements, whilst providing an overall representation of the intervention's feasibility.

### Data collection and management

Personal data will be handled and stored in accordance with General Data Protection Regulation and Coventry University's confidentiality and data protection policies. All data will be anonymised, and each participant following randomisation will be designated a unique trial ID. Data will be confidentially stored at UHCW, NHS Trust in a secure location and/or on password-protected computer drive. During the trial, monitoring will be completed frequently by research team members including the CI (FD). Following study completion, data will be archived for up to 5 years before all essential documentation is transferred to a third-party archiving service for a minimum of 3 years after the results have been publicly released or published.

